### Interim analyses {21b}

No interim analysis is planned.

### Methods for additional analyses (e.g., subgroup analyses) {20b}

Predictiveness of change in the main outcome and secondary outcomes regarding baseline, age, sex, education, disease-related factors (e.g., severity of motor symptoms), and (neuro)psychological factors (e.g., cognitive baseline level, self-efficacy, and depressive symptoms) is explored by adding both main effects and interactions with group to the model equation. Moreover, models are fitted in corresponding subgroups.

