Next to CT efficacy, feasibility, and acceptability, this study also seeks to provide exploratory analyses of possible predictors of CT responsiveness. Current studies indicate that cognitive baseline performance might be one of the most prominent CT predictors [38, 41, 49, 50]; other factors (e.g., sociodemographic, clinical, or (neuro)psychological) may also be relevant, but the body of literature is still inconsistent [51–53]. Determining who benefits most from CT can further help to identify an individualized, personal medicine approach that specifically targets the needs of individuals with PD, therefore complementing the previous two research goals.

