### Eligibility criteria {10}

To be included, participants must be diagnosed with idiopathic PD according to UK Brain Bank Criteria [57] and meet the criteria for advanced PD, defined as either meeting at least one of the established 5-2-1 criteria (five intakes of levodopa/day, 2 h of OFF time/day, and/or 1 h of troublesome dyskinesia/day) [58, 59] according to self-report or receiving pump therapy (i.e., intrajejunal levodopa pump [Duodopa, Lecigon, or subcutaneous Produodopa] or s.c. apomorphine pump [e.g., APO-go]). Participants who underwent deep brain stimulation (DBS) also have to fulfill the 5-2-1 criteria. Additionally, participants should have age-appropriate cognition/no cognitive impairment or mild cognitive impairment (PD-MCI) according to level 1 diagnosis (*MoCA* ≥ 21 points) [60] and maintain stable medication for 4-week pre-CT and through baseline and post-test. Participants, of any gender, must be 18 years of age or older, proficient in the German language, and have access to a computer, notebook, or tablet with Internet access. Exclusion criteria include a level 1 diagnosis of dementia (PDD; *MoCA* < 21 points) [60], severe depression (Beck Depression Inventory [BDI-II] ≥ 29 points) [61], epilepsy or other conditions with seizure-like manifestations and/or disorders of consciousness (ICD-10 G40), and any neurological, psychiatric, or acutely life-threatening disease that could impact cognition (according to a doctor’s letter or self-report).

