## Assignment of interventions: allocation

### Sequence generation {16a}

The allocation sequence was computer-generated with the help of a statistician (author [name]) using the website www.randomization.com. Allocation follows a stratified randomization procedure with permuted blocks of variable length. Participants are stratified by age (< 65 years vs. ≥ 65 years) and cognitive baseline level (*MoCA* ≤ 26 points vs. > 26 points).

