### Primary outcome

The primary outcome measure is the German version of the MoCA [56], a screening tool to detect MCI. The MoCA is a widely recommended screening tool for cognition in clinical trials [104]. The final score ranges from 0 to 30 points, with higher scores indicating better cognitive performance. Scores < 21 indicate PDD, scores from 21 to 25 indicate PD-MCI, and scores ≥ 26 indicate age-appropriate cognitive performance [60]. The MoCA has high sensitivity (90%) and specificity (87%) for detecting MCI [56, 60, 105] and has good reliability (Cronbach’s alpha of 0.83 [56]) and validity (receiver operating characteristics area under the curve 0.87 [106]).

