## Statistical methods

### Statistical methods for primary and secondary outcomes {20a}

The primary analysis is according to the intention to treat, with no exclusions. The change from baseline in the primary outcome MoCA is analyzed by a linear mixed model for repeated measures (MMRM) with fixed effects for baseline, group, time, and group × time interaction (ARH1-structured variance–covariance matrix over time). The primary comparison at T1 (week 9) is based on a pairwise contrast of estimated marginal means with a 95% confidence interval. Secondary outcomes (i.e., further timepoints and measures) are analyzed along the same line, however from an exploratory viewpoint only; thus, no multiplicity adjustment is required. Where available, observed changes will also be interpreted in relation to published minimally clinically important differences (MCIDs) to evaluate clinical relevance in addition to statistical significance.

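### With MoCA capped at 30, the planned baseline-by-group analysis will understate the training effect in high scorers whenever training works, and the plan has no check for this

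*Protocol article*

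**What the plan says.** All references are to the protocol article.

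- **Methods for additional analyses {20b}.** Predictiveness of change in the main outcome and the secondary outcomes, for factors that include baseline and cognitive baseline level, "is explored by adding both main effects and interactions with group to the model equation. Moreover, models are fitted in corresponding subgroups".
- **Statistical methods {20a}.** MoCA change from baseline is analysed by a linear mixed model with baseline as a fixed effect.
- **Primary outcome.** "The final score ranges from 0 to 30 points, with higher scores indicating better cognitive performance".
- **Eligibility criteria {10}.** "participants should have age-appropriate cognition/no cognitive impairment or mild cognitive impairment", with a lower MoCA limit of 21 and no upper limit.
- **Sequence generation {16a}.** Cognitive baseline level is a stratification factor, defined by MoCA and cut at 26 or below versus above 26.
- **Background and rationale {6a}.** On earlier research, "cognitive baseline performance might be one of the most prominent CT predictors". Predictors of responsiveness are the third study objective (Objectives {7}).

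The article does not mention a ceiling on MoCA, either in the analysis sections or among the limitations in the Discussion.

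**The concern.** Baseline MoCA would be tested as a modifier of change in the same bounded score. Someone entering at 21 can gain up to 9 points, someone at 27 up to 3, and someone at 30 none. In the trained arm, more high scorers reach 30 and have their gain cut off. The difference between arms is therefore compressed at the top of the scale and not at the bottom.

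This differs from regression to the mean, which affects both arms alike and drops out of the interaction with group. The ceiling does not drop out, because it bites harder in the arm that improves. The exploratory label does not address it either: that label guards against chance findings, whereas this is a bias in a known direction that a larger sample would not remove.

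At stake is the reading of the third objective. The Discussion hopes that predictor results may help to personalise training and allocate resources. An apparent weaker response in cognitively intact people could come from the scale.

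**Working it through.** **1. The plan's own figure.** The article gives no figure for the predictor analysis, only the sample size. With d = 0.5, two-sided 0.05 (sidedness assumed) and 80% power:

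n per arm = 2 × (1.960 + 0.842)² / 0.5² = 2 × 7.85 / 0.25 = 62.8, so 63 by the normal approximation and 64 by the exact t-test (power 0.801).

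This matches the stated 64 per arm, which is the size used below. For dropout, 128 / 0.9 = 142.2 and 128 × 1.1 = 140.8, both close to the stated 140.

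**2. Headroom, from the article's own numbers.** Headroom = 30 − baseline.

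- Baseline 21–26: 9 down to 4 points.
- Baseline 27–30: 3 down to 0 points.

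**3. Simulation set-up.** The article gives no MoCA mean, SD, retest error or practice gain, so these are assumptions.

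- Latent mean 25, 26 or 27; SD 3; reliability 0.83; retest gain 0 to 0.5 point in both arms. The article's 0.83 is Cronbach's alpha, and using it as retest reliability is itself an assumption.
- Scores are rounded and capped at 30; entry at 21 or more.
- The same true benefit for everyone, 0.75 or 1.25 points.
- Effect in a stratum = mean change in the trained arm minus mean change in the control arm.
- Interaction = coefficient of group × baseline in a linear regression of the post-test score on baseline, group and their product. With baseline in the model, using change as the outcome gives the same coefficient.

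**4. Results.** Ranges run over the assumed means and retest gains.

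| True effect, all participants | Estimated, baseline ≤ 26 | Estimated, baseline > 26 | Significant false interaction, 64 per arm |
|---|---|---|---|
| 0.75 | 0.74–0.76 | 0.44–0.61 | about 4–10% |
| 1.25 | 1.22–1.25 | 0.69–0.97 | about 7–26% |

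Shortfall above 26:

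- True effect 0.75: from 1 − 0.61/0.76 = 20% to 1 − 0.44/0.74 = 41%.
- True effect 1.25: from 1 − 0.97/1.25 = 22% to 1 − 0.69/1.22 = 43%.

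The interaction slope is −0.03 to −0.13 point per baseline point. With no training effect it is zero.

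**5. A second set of assumptions.** True SD 2.2, error SD 1.2, latent mean 25–27, practice gain 0 or 1 point.

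- Without a cap, the effects at ≤ 26 and > 26 are equal (for example 1.25 and 1.25) and the slope is about 0.
- With the cap and a 1.25-point benefit, they run from 1.25 versus 1.07 (14% lower) to 1.20 versus 0.66 (45% lower).
- With the cap and a 0.8-point benefit, they run from 0.80 versus 0.73 (9% lower) to 0.77 versus 0.45 (42% lower).
- The share at 29–30 at baseline is 8% for mean 25 and 28% for mean 27, and the artefact grows with it.
- False interactions are significant in 4–13% of trials at 0.8 point and 5–26% at 1.25 points.

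**6. Size against sampling noise.** At a true effect of 0.75, the spurious stratum difference is about 0.14–0.30 point. Taking a change SD of about 1.75 and strata of about 85 and 45, the standard error of an effect is 2 × 1.75/√85 = 0.38 and 2 × 1.75/√45 = 0.52. The standard error of their difference is √(0.38² + 0.52²) = 0.64 point.

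**7. Does the remedy work?** Under the assumptions of step 3, fitting the interaction with a model censored at 30 reduced the slope from between −0.03 and −0.13 to between 0.00 and −0.02.

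**The case against.** Several points on the other side stand.

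- **Secondary outcomes are covered.** A reader might infer that the predictor question rests on MoCA alone. It does not: the additional-analyses section covers main and secondary outcomes, so the same interaction is already planned for tests such as Trail Making, fluency, LPS 50+, digit span and BTA. What is missing is any use of those results to judge the MoCA interaction.
- **A false conclusion is not the likely result.** A reader might infer that the trial would probably declare cognitively intact people poorer responders. At 64 per arm the false interaction is seldom significant, and the spurious stratum difference is small against its standard error.
- **The size is assumed.** The article gives no MoCA distribution. With few participants near 30 and no practice gain, the shortfall can be as low as 9%.
- **The use is tentative.** A reader might infer that treatment allocation hangs on this analysis. The Discussion calls it exploratory and says only that it may help to tailor training.
- **The subgroup cut is not fixed.** The additional-analyses section names no threshold. The split at 26 is the stratification cut and is the natural reading, but it is an inference.

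It can also be said that a censored model is detail for an analysis plan that is not shown. That holds only in part. The article does fix the method, namely terms added to the linear model plus subgroup fits, and following it as written gives an estimate biased in a known direction.

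**Conclusion.** The point holds as a bias in exploratory estimates. If training works, and works equally for all, the planned linear MoCA analysis is expected to show a negative group-by-baseline interaction and an effect above 26 that is about 20–45% too small. This rests on latent mean 25–27, SD 3, reliability 0.83 and retest gain 0–0.5 point. The bias shrinks if few participants score near 30 and disappears if training has no effect, so the cap distorts who appears to respond but cannot create a response.

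With significance in about 4–26% of trials at 64 per arm, the practical risk is misreading interaction and subgroup estimates. The documents do not support the stronger reading that a false conclusion about cognitively intact people is likely. Nor does this point bear on the choice of primary analysis.

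**What to change.** In Methods for additional analyses {20b}, for MoCA as outcome and baseline cognition as predictor:

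1. Also fit the group-by-baseline interaction with a model for scores censored at 30, such as Tobit.
2. Report the share of participants scoring 29–30 by arm and stratum.
3. State that a smaller MoCA effect in high scorers is not read as lower responsiveness unless the censored model and the already planned interactions on the secondary cognitive tests point the same way.

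No new composite outcome is needed. The article gives no score ranges for the secondary tests, so the team should confirm which of them leave room at the top.

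The cost is a little more exploratory analysis of data already collected, reliance on the censored model's normality assumption, and a more cautious statement on predictors. The primary analysis, sample size and participant burden do not change.

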### Methods in analysis to handle protocol nonadherence and any statistical methods to handle missing data {20c}

A supplementary per-protocol analysis includes only patients with three valid assessments (i.e., at T0, T1, and T2) and essential adherence to the training schedule (i.e., ≥ 16/20 (80%) completed training days in the experimental group; all control participants). The sensitivity due to missing values of the primary analysis based on MMRM is investigated by reference-based multiple imputation (e.g., jump to reference) [108].

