**Fig. 1 Fig1:**
[figure not shown]
Overview of the 10 cognitive training exercises of the “HeadApp/NEUROvitalis Digital” program

To seamlessly incorporate the CT schedule into participants’ daily lives and accommodate symptom fluctuations or other daily activities, participants can flexibly choose their training days on a day-to-day basis. Once participants access the CT website, they are led to the home screen of the CT showing the first of three exercises for the current training day. Each new day the CT website is accessed, a new training day is unlocked, and the set of three exercises for the day is accessible successively within that day. During CT, participants may take breaks within an exercise (via a pause button) and between the exercises (before starting the next exercise) or may discontinue an exercise. In case of the discontinuation of an exercise, CT automatically guides participants back to the home screen, where they can then start the next scheduled exercise. After the completion of all three exercises, a notification appears on the home screen of the CT stating that no further exercises are scheduled for this day and inviting participants to return another day.

Participants are advised by the study team to complete all three scheduled exercises for a specific training day on time, i.e., until midnight of that same day. They are also instructed that they may take breaks between exercises and return to the CT later that same day. However, in the case where not all scheduled exercises can be completed within one training day, the non-completed exercises of that training day cannot be revisited another day. Instead, the CT program automatically transitions to the next training day featuring the next set of three exercises regardless of whether all exercises of the previous training day have been completed. Therefore, once the first exercise of a training day is started, participants have until midnight to complete the scheduled three exercises; otherwise, these exercises will no longer be accessible. This process is repeated for all 20 scheduled training days.

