#### Control group

To closely reflect clinical routine, participants of the CG continue their everyday life and care as usual after the baseline assessment. After a 5-week waiting period, participants complete the post-test in week 7 and the FU assessment at week 19. Following their FU assessment, participants receive 6 months of free-of-charge access to the CT program, including the CT schedule and the psychoeducational videos.

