#### CT feasibility and acceptability outcomes

Feasibility of the digital CT is assessed in terms of participants’ ability to complete the intervention as prescribed. Indicators include CT dropout rate, number of training days completed, total duration of training, and technical handling, including any problems encountered during CT intervention. These data are collected from the CT software and via a pen-and-paper CT diary distributed to participants of the EG after their baseline assessment. Based on current literature, the CT intervention is considered feasible if CT dropouts are ≤ 14% [43] and participants completed at least 80% (i.e., ≥ 16/20) of the training days and the total training duration (i.e., ≥ 720/900 min) [30, 84]. Via optional free-text comments in the CT diary, participants can give qualitative feedback on technical handling of the CT (cf. next paragraph).

CT acceptability is evaluated based on participants’ experience with the CT. In the pen-and-paper CT diary, daily ratings capture the motivation to engage in CT on a 5-point scale (0 = “not motivated at all,” 5 = “highly motivated”) and satisfaction with each session (0 = “not good at all,” 5 = “very good”). Weekly ratings assess how well participants were able to integrate CT into their daily routines and the extent to which external factors, such as tiredness or stress, impacted training (0 = “not at all,” 5 = “very much”). At the end of the CT intervention, participants provide an overall evaluation using the German grading system (1 = “very good,” 6 = “unsatisfactory”) and indicate if they would recommend the CT (“yes”/“no”). Optional free-text comments are collected after each session, weekly, and in the final evaluation to capture qualitative feedback. The intervention is considered acceptable if the average scores across CT sessions and weekly ratings are ≥ 4/5 points and the overall evaluation reaches a score of ≥ 3.5/6 points according to the German grading system. Additionally, if more than 80% of participants recommend the CT, it will be considered acceptable. If the criteria for feasibility and acceptability are not met, the results of the CT efficacy should be interpreted cautiously as the intervention may not have been delivered effectively.

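### The per-protocol analysis filters only the training arm on adherence and requires the T2 visit even for the T1 contrast, so it is a non-randomised comparison that discards usable data

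*Protocol article*

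**What the plan says.** Section {20c} defines the only adherence analysis in the article: "A supplementary per-protocol analysis includes only patients with three valid assessments (i.e., at T0, T1, and T2) and essential adherence to the training schedule". The adherence condition is then spelled out as "≥ 16/20 (80%) completed training days in the experimental group; all control participants". Valid T0, T1 and T2 assessments are thus required in both arms, and adherence in one.

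Four other places bear on this:

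- **Statistical methods {20a}:** the primary analysis is intention to treat without exclusions. It uses a mixed model for repeated measures with baseline as a fixed effect, and the primary contrast is at T1.
- **CT feasibility and acceptability outcomes:** feasibility asks that "participants completed at least 80% (i.e., ≥ 16/20) of the training days and the total training duration (i.e., ≥ 720/900 min"), together with a ceiling on dropouts. The minutes condition does not appear in {20c}.
- **Intervention description {11a}:** a day's unfinished exercises cannot be made up, and the software moves on "regardless of whether all exercises of the previous training day have been completed".
- **Control group:** access to training comes only at the end: "Following their FU assessment, participants receive 6 months of free-of-charge access to the CT program".

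**The concern.** Reaching 16 training days happens after randomisation and may depend on health. The protocol itself makes this plausible. The Background says that complications and functional or affective impairment could influence motivation and the motor skills to train. The Discussion lists symptom fluctuations that may affect the ability to complete CT. If those who keep training would have had better MoCA scores at T1 anyway, comparing them with all controls credits that difference to CT.

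The T2 condition is a separate matter. A participant who trained fully and has valid T0 and T1 assessments, but misses the follow-up visit, leaves the set even when the question concerns T1. This sits badly with section {18b}, which says that data collected before a dropout or a missed assessment are still used.

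At stake is the only evidence the trial plans on the effect in people who actually trained. The confirmatory result does not depend on it.

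**Working it through.** **Plan's own figures.** The article gives no figure for the per-protocol analysis. For scale, section {14} states d of 0.3 to 0.5, 80% power, alpha 0.05 and 64 per group. A two-sided two-sample t-test (sidedness assumed) gives 64 per group at d = 0.5, with power 0.801. At d = 0.3 it gives 176 per group. The planned number therefore matches the upper end of the stated range. With 70 randomised per arm and 10% dropout, 70 × 0.9 = 63 per arm remain.

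**EG-only filter, no true effect.** Assume that the EG members retained are the top fraction p on a latent tendency to adhere. Let r be the correlation of that tendency with the T1 outcome. Baseline MoCA is in the model, so r should be read as what remains after baseline. With c = z(1−p) and m = φ(c)/p:

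bias = r × m, in SD units.

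For p = 0.70, c = −0.524, φ(c) = 0.348 and m = 0.348/0.70 = 0.497. Approximate two-sided type I error uses 63 controls and 63p in the EG, with SE = √(v/(63p) + 1/63) and v = 1 − r²m(m − c). For p = 0.70 and r = 0.3: v = 0.954, SE = √(0.954/44.1 + 1/63) = 0.194, bias/SE = 0.149/0.194 = 0.77, error 0.120.

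| EG retained (assumed) | r | Bias (SD) | Type I error |
|---|---|---|---|
| any | 0 | 0 | 0.050 |
| 86% | 0.1 | 0.026 | 0.052 |
| 86% | 0.3 | 0.078 | 0.071 |
| 80% | 0.1 | 0.035 | 0.054 |
| 80% | 0.3 | 0.105 | 0.087 |
| 70% | 0.1 | 0.050 | 0.057 |
| 70% | 0.3 | 0.149 | 0.120 |

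At 70% retained, 0.05 to 0.15 SD is 17 to 50% of d = 0.3 but 10 to 30% of d = 0.5, the effect that 64 per group corresponds to.

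**T2 requirement.** Apply the same formula to both arms with r = 0.3:

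- 90% completion in each arm: 0.
- 85% in the EG and 95% in controls: 0.082 − 0.033 = +0.05 SD.
- The reverse: −0.05 SD.

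The sign depends on which arm loses more people, which is not known in advance. The loss of T1 data is certain for anyone with T1 but no T2; the documents do not say how many to expect.

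**Days against minutes.** 16 × 45 = 720 minutes, so the two criteria agree when every exercise of 16 days is done in full. A stricter rule that retained fewer people would select more strongly: at r = 0.3 the bias is 0.105 SD at 80% retained and 0.149 SD at 70%.

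**Complier effect.** Controls have no access to the program until after follow-up, so non-compliance is one-sided. The complier effect at T1 is the intention-to-treat contrast divided by the EG share who adhere, provided that EG members below the cut gain nothing. If they gained as much as adherers, the estimate would be too large by 1/0.8 = 1.25 to 1/0.7 = 1.43.

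**The case against.** The strongest reply is that the analysis is labelled supplementary, that the primary analysis excludes nobody, and that a passive control group has no training days to filter on. All of that stands, and it limits the weight of the point. It does not make the comparison randomised. One could also say that a single set with three visits keeps the same people at both time points. That is a convenience, and it does not justify discarding T1 data for a T1 estimate.

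A reader might infer more than the documents support:

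- **That the analysis is biased toward CT, or would look favourable even if CT did nothing.** This needs a positive r beyond baseline. No correlation is given, and at r = 0 the bias is zero.
- **That all the features push the same way.** The T2 rule has no fixed direction, and a days-only rule selects less than a days-and-minutes rule.
- **That 16 days could mean only 240 minutes (16 × 15).** This counts a day with one exercise done as completed. Section {11a} describes a training day as three exercises, so the natural reading of a completed day gives 720 minutes, apart from discontinued exercises.
- **That {20c} contradicts the feasibility criterion.** One defines an analysis set and the other a benchmark for judging the intervention; they may differ.

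The complier analysis also has a fair objection against it. EG members below the cut may benefit from partial training or from the psychoeducational videos, which violates its key assumption.

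**Conclusion.** The point holds in limited form. The per-protocol set breaks the randomised comparison by selecting in one arm only, and it could favour CT if adherers have the better prognosis. Its size is illustrative: 0 at r = 0, and about 0.05 to 0.15 SD at r = 0.1 to 0.3 with 70% retained, less with higher retention. Both r and the retention are assumptions. The T2 condition needlessly discards T1 data in a model that can use incomplete cases, and any bias from it is of unknown sign. I take the per-protocol analysis to use the primary model, since {20c} names no other. The difference between the days rule and the days-and-minutes criterion calls for reconciliation in the complier analysis and is not itself a source of bias toward CT. The primary result is untouched.

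**What to change.** 1. For the T1 contrast, require only T0 and T1. Require T2 only for the T2 contrast.
2. Report the per-protocol result as a descriptive, non-randomised comparison.
3. Add a complier-average causal effect at T1 with randomisation as the instrument and the primary model's baseline covariate. Give a version with training minutes as the dose, as a check.
4. For the complier analysis, define adherence consistently with the feasibility criterion (days and minutes) and say what counts as a completed day. Do not add the 720-minute condition to the per-protocol filter, because that could strengthen the selection.
5. State the exclusion restriction and why it may fail. The minutes version addresses partial training, at the price of an assumed dose-response shape. It does not address the videos, which can act without any training minutes.

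The cost is some extra analysis of data already being collected. The complier estimate will have a wider interval than the intention-to-treat contrast and rests on an assumption that can be argued but not tested.
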